## Abstract

**Background:**

Suicide, attempted suicide and suicidal thoughts are major public health problems worldwide. Effective face-to-face treatments are Cognitive Behavioural Therapy (CBT), Dialectical Behavioural Therapy (DBT) and Problem Solving Treatment (PST). However, about two-thirds of persons who die by suicide have not been in contact with mental health care services in the preceding year, and many have never been treated. Furthermore, many patients do not disclose their suicidal thoughts to their care provider. This may be out of shame, due to fear of stigma or due to lack of trust in (mental) health care. Since many suicidal individuals seek information online, the internet provides an opportunity to reach suicidal individuals who would not be contacted otherwise. By providing a self-help intervention online, persons can anonymously learn to gain control over their suicidal thoughts. There is convincing evidence that self-help is effective for a number of mental disorders. In this study the effectiveness for suicidal thoughts is examined.

**Methods/Design:**

In this study, a recently developed self-help intervention will be evaluated in a Randomized Controlled Trial. The intervention is based on Cognitive Behavioural Therapy and is aimed at subjects who experience mild to moderate suicidal thoughts. This is defined as a score between 1 and 26 on the Beck Scale for Suicidal Ideation (BSS). Higher and lower scores are excluded. In addition, severely depressed subjects are excluded. In total, 260 subjects will be randomly allocated to the intervention-condition (N = 130) or to the information-control condition (N = 130). Self-report questionnaires will be filled out at baseline, 6 weeks after baseline and 18 weeks after baseline. Primary outcome measure is the reduction in frequency and intensity of suicidal thoughts. Secondary outcome measures are the reduction of hopelessness, anxiety and depression, sleeplessness, worry and quality of life measures.

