#### Secondary outcome measures

Secondary outcome measures include depressive symptoms, hopelessness, anxiety symptoms, worrying, quality of life and costs related to health care utilization and production loss.

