##### Quality of life

The *EuroQol *(EQ-5D) [51] is a standardised non disease specific instrument for describing and valuing health related quality of life. It consists of five items (mobility, self-care, usual activities, pain/discomfort and anxiety/depression). Each item is rated as 'no problem' (1), 'some problem' (2), or 'extreme problem' (3). The resulting health state can therefore be expressed by a five-digit number. In addition, it is required to rate current health state on a thermometer ranging from 0 (worst imaginable health state) to 100 (best imaginable health state).

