##### Costs: health care utilization and production loss

Health care utilization and production loss are evaluated by means of the *Trimbos/iMTA questionnaire for Costs associated with Psychiatric Illness *(TiC-P) [52]. The TiC-P consists of two different parts that can be administered separately. Part I is concerned with measuring the direct costs of care consumption of subjects with psychiatric disorders. It consists of 15 items, but can be customized for the study population. Items that are considered irrelevant can be left out. Part II is meant to determine indirect costs resulting from production loss associated with psychiatric disorders. It consists of the *Short Form Health and Labor Questionnaire *(SF-HLQ) [53]. The SF-HLQ contains three modules covering absence from paid employment, production loss without absence from paid employment and impediments to paid of unpaid employment.

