##### Functioning

The *Work and Social Adjustment Scale *(WSAS) [54] measures impaired functioning attributable to an identified problem. It is a five item scale, with each item being rated on a 0 (no impairment at all) to 8 (very severe impairment) scale. The WSAS is valid and reliable. Internal consistency ranges from 0.70 to 0.94. Test-retest correlation was 0.73.

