### Statistical analyses

To test the hypothesis that the self-help intervention is superior to the control condition, the analysis will be conducted on an Intention to Treat basis following the pertinent BMJ & Consort guidelines. Missing observations at follow up will be imputed by regression imputation or multiple imputations, stratified for predictors of outcome and loss to follow-up. Relative improvements in frequency and intensity of suicidal thoughts in the experimental group in comparison with the control group will be calculated by Cohen's *d*. For this confirmatory analysis the primary outcome measure is used (BSS). To the exploratory analyses of the secondary outcome measures, a Bonferroni correction will be applied to control the overall Type I error rate.

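### The lists of secondary outcomes disagree, so the family for the Bonferroni correction is inconsistent; Holm's procedure would be a free improvement once one list is fixed

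*Protocol article*

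**What the plan says.** The protocol article describes the secondary outcomes in three places.

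- The abstract, under Methods/Design: "Secondary outcome measures are the reduction of hopelessness, anxiety and depression, sleeplessness, worry and quality of life measures".
- The Secondary outcome measures section: "Secondary outcome measures include depressive symptoms, hopelessness, anxiety symptoms, worrying, quality of life and costs related to health care utilization and production loss".
- The instrument entries that follow: BDI-II, BHS, HADS-A, PSWQ-PW, EQ-5D, TiC-P and, under Functioning, the WSAS, which "measures impaired functioning attributable to an identified problem".

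Statistical analyses ties an error-rate rule to this set: "To the exploratory analyses of the secondary outcome measures, a Bonferroni correction will be applied to control the overall Type I error rate". The same section keeps the primary test apart: "For this confirmatory analysis the primary outcome measure is used (BSS". The article gives neither a number of secondary tests nor an adjusted significance level.

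**The concern.** Three descriptions of one set should name the same members, and these do not. A reader of the abstract expects a sleep result for which the article describes no measure, and does not learn that costs are an outcome. A reader of the methods list does not learn that functioning is one.

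The mismatch has a statistical consequence because Bonferroni divides 0.05 by the number of tests. If the members are inconsistent, so is the family over which the overall error rate is to be controlled. Fixing the list also gives an occasion to ask whether plain Bonferroni is the best way to spend the 5%.

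**Working it through.** **Step 1: members.** The three descriptions side by side:

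| Domain | Abstract | Secondary outcome measures | Instrument described |
|---|---|---|---|
| Depression | yes | yes | BDI-II |
| Hopelessness | yes | yes | BHS |
| Anxiety | yes | yes | HADS-A |
| Worry | yes | yes | PSWQ-PW |
| Quality of life | yes | yes | EQ-5D |
| Sleeplessness | yes | no | none |
| Costs | no | yes | TiC-P |
| Functioning | no | no | WSAS |
| **Count** | **6** | **6** | **7** |

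The union has 8 domains. Costs are counted once here. Five domains agree in all three places and three do not.

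**Step 2: threshold.** The article states no adjusted level, so there is no figure to reproduce. With k tests the Bonferroni level is 0.05/k:

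- k = 6: 0.05/6 = 0.0083
- k = 7: 0.05/7 = 0.0071
- k = 8: 0.05/8 = 0.0063 (0.00625 before rounding)

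**Step 3: what the difference in k costs.** Inputs from the article are 100 per condition, d = 0.35, 130 randomised per arm and 30% drop-out (Sample size; abstract). The article gives d = 0.35 for the primary outcome only, so using it for each secondary outcome is an assumption. A two-sided test and one test per outcome are also assumed. Power is approximately Φ(d√(n/2) − z), with z the normal quantile at 1 − 0.05/(2k).

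For n = 100, d√(n/2) = 0.35 × √50 = 2.475. With 130 × 0.70 = 91 completers, it is 0.35 × √45.5 = 2.361.

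| k | z | Power, n = 100 | Power, n = 91 |
|---|---|---|---|
| 6 | 2.638 | 43.5% | 39.1% |
| 7 | 2.690 | 41.5% | 37.1% |
| 8 | 2.734 | 39.8% | 35.4% |

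From k = 6 to k = 8 the loss is 43.5 − 39.8 = 3.7 points at n = 100, and also 39.1 − 35.4 = 3.7 points at n = 91.

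**Step 4: Holm against Bonferroni.** Holm orders the p-values and compares the smallest with 0.05/k, the next with 0.05/(k − 1), and so on, stopping at the first failure. Every Bonferroni rejection is therefore also a Holm rejection. The size of the gain comes from simulation: 200,000 runs, two-sided tests, equicorrelated normal test statistics with assumed correlation 0.5, and d = 0.35 for each real effect. The figures are average power over the real effects.

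| k, real effects | n per arm | Bonferroni | Holm | Gain (points) |
|---|---|---|---|---|
| 6, all | 100 | 43.5% | 52.6% | 9.1 |
| 7, all | 100 | 41.4% | 50.5% | 9.2 |
| 6, all | 91 | 39.2% | 47.6% | 8.4 |
| 7, all | 91 | 37.1% | 45.5% | 8.4 |
| 6, three | 100 | 43.4% | 45.9% | 2.5 |
| 7, three | 100 | 41.5% | 43.5% | 2.0 |
| 6, three | 91 | 39.1% | 41.3% | 2.3 |
| 7, three | 91 | 37.1% | 38.9% | 1.8 |

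Gains were taken before rounding. Familywise error was at or below 0.05 for both procedures in every scenario.

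**The case against.** The strongest case against is that this is mainly editorial. Both published lists have six domains, so each gives 0.0083. The methods list is worded as non-exhaustive and the WSAS stands under the secondary-outcome heading, so its status can be guessed. The analyses are called exploratory, and the confirmatory test is the BSS alone. Bonferroni does what the plan asks of it. Holm also needs a defined family, so it does not repair the inconsistency.

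Most of this stands, and it limits the size of the point. It does not remove the contradiction: equal counts with different members are still different families, and the sentence that calls the analyses exploratory also promises control of the overall error rate.

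A reader might infer more than the article supports:

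- **A divisor of nine.** The EQ-5D section adds a second rating ("In addition, it is required to rate current health state on a thermometer ranging from 0"), and on costs the article says "The TiC-P consists of two different parts that can be administered separately". Nine tests would require both instruments to be split into two tests each, and no section says that they will be.
- **A threshold chosen after the data are seen.** The analysis plan is not shown. The number of tests, the EQ-5D score and the time point (6 or 18 weeks) are commonly fixed there, so their absence from a condensed article is not a finding.
- **Sleep is not measured and must be withdrawn.** The article shows only that no sleep instrument is described in it. The full protocol may have one.
- **Costs should leave the tested family.** Nothing in the article makes their inclusion an error. It only leaves their place unclear.
- **Bonferroni is a mistake.** It is valid, and it gives simple simultaneous confidence intervals, which Holm does not.

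**Conclusion.** The inconsistency is real and lies within the article, so no further document can make these sections agree as written. Sleeplessness has a place in the abstract but no instrument, costs are missing from the abstract, and functioning is missing from both lists. The family is six, seven or eight depending on the section read, and the threshold runs from 0.0083 to 0.0063. At an assumed d of 0.35 this moves power per outcome by about 4 points, so clarity about which outcomes are tested matters more than the threshold.

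Holm is an optional improvement, not the correction of an error. Its gain of about 8–9 points holds only if every secondary outcome has a real effect of the assumed size, and it falls to about 2–3 points if about half do. These figures rest on d = 0.35 for secondary outcomes, correlation 0.5, two-sided testing and one test per outcome, none of which the article states. The primary BSS analysis is unaffected.

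**What to change.** 1. Use one list of secondary outcomes in the abstract, in Secondary outcome measures and in the instrument entries. Either name the sleep measure or drop sleeplessness, according to what is actually collected. Add functioning (WSAS) to both lists. Add costs to the abstract, and state whether they belong to the tested family or are only reported.
2. State in Statistical analyses that the correction covers that list, and give the number of tests.
3. Optionally, replace Bonferroni with Holm's step-down procedure in the same sentence. With six tests the ordered p-values would be compared with 0.0083, 0.0100, 0.0125, 0.0167, 0.0250 and 0.0500.

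Items 1 and 2 change wording only and need no new data, though one promised outcome is withdrawn if no sleep measure exists. Item 3 costs only the simple simultaneous confidence intervals that go with Bonferroni. If those intervals are wanted, keeping Bonferroni is defensible.

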**Discussion:**

This study is the first to evaluate the effectiveness of a web-based self-help intervention for suicidal thoughts. Several limitations and strengths of the design are discussed.

**Trial Registration:**

Netherlands Trial Register, NTR1689

## Background

Suicide, suicidal behaviour and suicidal thoughts are major public health problems worldwide. In the Netherlands, around 1500 persons die by suicide each year, which accounts for 1% of all deaths [1]. In addition, an estimated 120.000 suicide attempts occur each year [2]. The lifetime prevalence of suicidal thoughts in the adult Dutch population is estimated to be 11% [3]. Suicidal behaviours generally are preceded by suicidal thoughts. A population-based study in the USA showed that 34% of individuals with suicidal thoughts developed specific suicide plans, while 26% directly proceeded to an attempt. In addition, 72% of those who developed a plan proceeded to an attempt [4]. In order to prevent suicidal plans and behaviours, prevention should be aimed at suicidal thoughts.

The majority of persons with suicidal thoughts (80%-82%) meet the criteria of a psychiatric disorder [5]. Most prevalent is depression. Suicidal thinking is one of the most severe symptoms of depression and is characterised by extreme negative thoughts about the self. It has been suggested that relapse in both depression and suicidality is attributed to 'cognitive reactivity' [6,7]. This means that once suicidal thoughts are experienced during an episode of depression, the likelihood that such thoughts will reoccur in a subsequent episode may be increased [8,9]. This 'Differential Activation Theory' of suicidality underlines the importance of aiming prevention at an early stage of the suicidal development.

Many suicidal individuals are reluctant to disclose their suicidal thoughts to others and to seek help. An international review showed that two-thirds were not in contact with mental health care services within the year before the suicide [10]. In the Netherlands, this is estimated to be 64% [11]. An explanation could be that many adults who experience suicidal thoughts do not perceive a need for care [12]. Moreover, there seems to be a negative relationship between levels of suicidal thoughts and help-seeking [13]. Factors that contribute to this 'help-negation effect' may be shame, fear of stigma, lack of trust in mental health care, and prejudices about health care providers. Bearing this in mind, suicidal individuals could benefit from accessible, anonymous help. The internet can play an important role in providing this.

The internet has become an important source of information and means of communication. Worldwide, around 23.5% of the population has access to the internet [14]. Dutch internet access is among the highest in the world (91%) [1]. In general, it has been found that persons with stigmatizing psychiatric illnesses are likely to use the internet to access health information and to communicate with professionals about their condition [15]. The anonymity of the internet may be an important explanation for this [16]. Overall, the internet could be an effective tool in reaching individuals with suicidal thoughts who would not be reached otherwise, or would come into contact with mental health care in a late phase of their suicidal process. For suicidal persons who are being treated, it could be an additional source of help.

Worldwide, there are numerous suicide-related websites. In 2007, a search for English suicide-related websites showed that 13% of the retrieved websites was aimed at prevention or support [17]. An inventory of Dutch suicide-related websites revealed a similar percentage that was aimed at prevention [18]. In general, not much is known about the quality of suicide prevention websites and scientific evaluation of the effectiveness of such websites is lacking. It is therefore not well established what effects prevention websites may have on suicidal individuals.

Although a substantial number of individuals with suicidal thoughts do not seek help, effective treatments exist. Evidence about effectiveness is currently available for Cognitive Behavioural Therapy (CBT), Dialectical Behaviour Therapy (DBT) and Problem Solving Treatment (PST) [19-24]. However, these studies only include face-to-face treatments. In other mental disorders it has been shown that treatments do not necessarily have to be delivered in face-to-face format. Particularly CBT can also be effectively delivered in a self-help format (either a book or through the Internet). Self-help therapy can be defined as a standardized psychological treatment that the patient works through independently at home. Numerous randomized trails have shown that self-help is effective in reducing depressive symptoms, symptoms of anxiety, problem drinking, social phobia and health problems such as headache [25-28]. For suicidal thoughts, a few self-help books are available, but these have not been scientifically evaluated. To our knowledge, no Internet self-help treatments for suicidal thoughts are yet available.

In summary, prevention should be aimed at the onset of suicidal thoughts. The internet can facilitate accessible interventions that may reach suicidal individuals who would not be reached otherwise. In this study, the effectiveness of a recently developed web-based self-help intervention for suicidal thoughts is evaluated in a randomized controlled trial.

## Methods/Design

### Design

This study is a randomized controlled trial comparing a web-based self-help intervention with a waitlist control condition. The intervention is aimed at persons with mild to moderate suicidal thoughts. Subjects in the control condition will have access to an information website and will start the intervention after the experimental group has finished (i.e. after six weeks). Assessments will take place at baseline, 6 weeks after baseline and 18 weeks after baseline.

This study was approved by the Medical Ethics Committee of the VU University Medical Centre (registration number 2008/204).

### Sample size

The sample size of this study is based on the expected effect on the primary outcome measure, i.e. the reduction in frequency and intensity of suicidal thoughts. In order to be able to demonstrate a clinically relevant effect-size of 0.35 with α = 0.05 and β = 0.80, 100 subjects are needed in each condition. When including an expected drop-out of 30%, the total sample size is determined at 260. The effect-size of 0.35 is based on effect-sizes found in other studies into internet interventions, mainly for depression [28,29].

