## Discussion

This paper describes the study protocol of a randomized controlled trial comparing a web-based self-help intervention to reduce suicidal thoughts with a control condition. To our knowledge, this is the first self-help application targeted specifically at suicidal thoughts. This aspect simultaneously might give rise to the idea that focusing mainly on suicidal thoughts could instigate suicidal thoughts or even suicidal behaviour. Even though this is a widespread belief, this idea is not validated in psychology or psychiatry [55].

The described study design has several methodological limitations. First, internet interventions in general and self-help applications in particular are subjected to high attrition rates [56]. Dropout from the study (dropout attrition) can introduce a selection bias and therefore be a threat to validity. In order to reduce dropout attrition, the questionnaires are presented separately from the intervention website and reminders are sent. Dropout from the intervention (nonusage attrition) may result in an underestimation of the effect size. In order to reduce nonusage attrition, subjects receive a motivating (automated) e-mail each week. Besides trying to reduce attrition, it will be analysed thoroughly (as has been suggested by Eysenbach) [56].

Second, anonymous participation is not possible because subjects are at risk for suicide, and we wanted to be able to monitor them and take action if necessary. As a result, the study population may differ from the target population. In order to identify possible differences, several demographics are obtained before registration.

Finally, no diagnostic interview is conducted. This makes it impossible to diagnose psychiatric disorders, but is in keeping with the self-help character of the intervention. It is also in accordance with the eventual purpose of use, since the intervention will become available for people with suicidal thoughts in general, irrespective of the presence of a possible psychiatric disorder. A feature of the described design that decreases the generalizability to this target group, is that severe suicidal and severe depressed subjects are excluded. The rationale for this is that they need more extensive care.

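### The 100 subjects per condition match 80% power for d = 0.35 under a one-sided 5% test that is never declared; a two-sided unadjusted test has about 69%

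*Protocol article*

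**What the plan says.** The Sample size section bases the calculation on the primary outcome, the Beck Scale for Suicide Ideation (BSS). It states that for an "effect-size of 0.35 with α = 0.05 and β = 0.80, 100 subjects are needed in each condition", and it describes this effect as clinically relevant. It continues: "When including an expected drop-out of 30%, the total sample size is determined at 260". The abstract splits the 260 equally, 130 per condition.

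The section does not say whether the 5% level is one-sided or two-sided. The Statistical analyses section introduces the test with "To test the hypothesis that the self-help intervention is superior to the control condition" and expresses the group difference as Cohen's d. It names no sidedness either. Neither section gives a baseline-outcome correlation or a baseline-adjusted variance as a basis for the sample size.

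**The concern.** A reader who meets a bare α = 0.05 will normally take it as two-sided. On that reading the stated number does not deliver the stated power: it falls short by about 30 subjects per condition, or about 11 percentage points of power. This matters because the figure supports the confirmatory test of the primary outcome. If the true effect is d = 0.35 and 100 subjects per condition are analysed, a two-sided test misses it about 31% of the time, where the plan implies 20%. A null result would then carry less weight against d = 0.35 than the plan suggests.

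The label on the power is also wrong. β is the type II error rate, so 80% power corresponds to β = 0.20.

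**Working it through.** **Inputs.** From the Sample size section: d = 0.35 (SD = 1), α = 0.05, power 0.80 (printed as β), 100 per condition, 30% drop-out, total 260. From the abstract: 1:1 allocation. Sidedness is not given, so both cases are computed.

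**Formula.** For two independent means, n per arm = 2(z_α + z_power)² / d², with z_power = 0.842 and d² = 0.1225.

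**Reproducing the plan's figure (one-sided 5%).** 2(1.645 + 0.842)² / 0.1225 = 100.9, so 101 per arm. The t-test version gives 101.6, so 102. The stated 100 is reproduced to within one or two subjects.

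**Two-sided 5%.** 2(1.960 + 0.842)² / 0.1225 = 128.1, so 129 per arm. The t-test version gives 129.1, so 130. The stated 100 is not reproduced.

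**Power for d = 0.35.** The non-centrality is 0.35 × √(n/2), and power is approximately Φ(non-centrality − z_α). At n = 100 the non-centrality is 2.475: two-sided Φ(2.475 − 1.960) = 0.697, one-sided Φ(2.475 − 1.645) = 0.797.

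The drop-out case follows from 260 × 0.70 = 182, or 91 per arm. (The total of 260 is 200 × 1.3; dividing instead, 200 / 0.70, gives 286. That is a separate matter, but it explains why 91 remain and not 100.)

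| Analysable per arm | Two-sided, normal / t | One-sided, normal / t |
|---|---|---|
| 91 | 65.6% / 65.1% | 76.3% / 76.0% |
| 100 | 69.7% / 69.2% | 79.7% / 79.4% |
| 130 | 80.6% / 80.3% | 88.0% / 87.9% |

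**Effect detectable with 80% power, two-sided.** d = 2.802 × √(2/n). At n = 100 this is 0.396 (t-based 0.398), so 0.40. At n = 91 it is 0.415, so 0.42.

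**Could a baseline-adjusted, two-sided test give 100?** With ANCOVA the requirement is multiplied by 1 − r², where r is the assumed baseline-outcome correlation:
- r = 0.30: 128.1 × 0.910 = 116.6, so 117
- r = 0.47: 128.1 × 0.779 = 99.8, so 100
- r = 0.54: 128.1 × 0.708 = 90.7, so 91

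A correlation of about 0.47 would therefore also lead to 100 per arm. The article states no such correlation for the sample size.

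**The case against.** **The figure is not a miscalculation.** This stands. The 100 reproduces under a one-sided 5% test, and the hypothesis is worded directionally. A directional hypothesis does not fix the sidedness of a test, however, since superiority is routinely tested two-sided. A condensed article may also leave sidedness to a fuller document. But the article does publish a number needed for a stated α and power, and that number holds only under a choice it does not disclose.

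**A one-sided test is not the only route to 100.** This also stands. The primary outcome is a reduction, which refers to baseline, and the Suicidal thoughts subsection quotes a BSS test-retest correlation of 0.54. A two-sided ANCOVA with r of about 0.47 would need about 100. But the 0.54 appears as a reliability figure and not as a design input; used in an ANCOVA it would give 91, and used for a simple change score 128.1 × 2 × (1 − 0.54) = 117.9, so 118. The route is possible but unstated.

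**Stronger readings that the article does not support.**
- A reader might infer that the authors' own expectation of harm rules out a one-sided test. The Discussion does mention the idea that "focusing mainly on suicidal thoughts could instigate suicidal thoughts or even suicidal behaviour", but it goes on to say that this belief has not been validated. The sentence is not evidence that the authors expect harm, and the point here does not rest on it.
- A reader might infer that the roughly 1-in-3 chance of missing d = 0.35 applies before any drop-out. It does not: 100 is the number before the drop-out allowance is added, that is, the analysable number. With all 130 per arm observed, two-sided power is about 80%. The article, however, plans for 30% loss.
- Taken literally, β = 0.80 would mean 20% power. The calculation shows that 80% power was used, so this is a labelling slip that does not affect N.

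**Conclusion.** The point holds as one of undeclared sidedness and misstated power. For an unadjusted two-group comparison at d = 0.35, the claim of 80% power with 100 per condition is approximately true one-sided (79%) and untrue two-sided (69%, with 129 to 130 per condition needed). At the article's own drop-out rate the two-sided figure is about 65% and the one-sided figure about 76%.

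These results assume equal arms, equal variances, no baseline adjustment, and no recovery of information by imputing the missing outcomes. A baseline-adjusted two-sided analysis could make 100 adequate if the correlation is about 0.47 or higher, but that would be a new assumption, not the stated basis.

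**What to change.** Rewrite the Sample size paragraph; N stays at 260.

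1. State whether α = 0.05 is one-sided or two-sided.
2. Replace β = 0.80 by power (1-β) = 0.80.
3. Restate the power to match the choice:
   - **Two-sided, unadjusted:** about 69% for d = 0.35 with 100 analysable per condition (80% for d = 0.40), and about 65% with the 91 per condition expected after 30% drop-out (80% for d = 0.42).
   - **One-sided 5%, if that was intended:** declare it, justify it, and give about 79% at 100 and 76% at 91 per condition.
   - **Baseline-adjusted, if that was intended:** name the analysis and the assumed baseline-outcome correlation, and give the power that follows.

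The cost is wording only. Under a two-sided unadjusted test the published power becomes less favourable, but allocation, outcome and enrolment do not change.

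### The 30% drop-out allowance multiplies by 1.3 instead of dividing by 0.7, so 260 randomised leaves about 91 observed outcomes per arm, not the stated 100; the slip itself costs 3 to 4 power points

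*Protocol article*

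**What the plan says.** The Sample size section sets the requirement in one sentence: "clinically relevant effect-size of 0.35 with α = 0.05 and β = 0.80, 100 subjects are needed in each condition". The value printed as β can only sensibly be read as power of 80%. Sidedness is not stated. The next sentence adds the allowance for attrition: "When including an expected drop-out of 30%, the total sample size is determined at 260". The Methods/Design part of the Abstract confirms the total and the equal split: "260 subjects will be randomly allocated to the intervention-condition (N = 130) or to the information-control condition (N = 130". No other drop-out rate or inflation rule appears.

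The Statistical analyses section plans an intention-to-treat analysis and says: "Missing observations at follow up will be imputed by regression imputation or multiple imputations". The Sample size section does not use imputation to justify 260.

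**The concern.** Three printed figures do not fit together: 100 needed per arm, 30% expected to drop out, and 260 in total. A drop-out rate applies to those randomised, so the required number must be divided by the retained fraction, 0.7. The plan appears to have added 30% of the required number instead.

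A reader of the section will take it that a 30% loss still leaves 100 observed outcomes per arm, and it does not. The allowance protects against a risk that the article treats as serious: the Discussion names attrition as its first limitation, and the Inclusion procedure is built partly to reduce it. At exactly the rate the plan expects, the allowance falls short, and a null result would then be read against more power than the design has.

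**Working it through.** **Inputs.** From Sample size: effect size d = 0.35, α = 0.05, power 0.80 (printed as β), 100 per arm (200 in total), drop-out 30%. From the Abstract: 260 randomised, 130 per arm.

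**Step 1. Reproduce the plan's total.**
- Required × (1 + drop-out) = 200 × 1.3 = 260. This matches exactly.
- Required ÷ (1 − drop-out) = 200 ÷ 0.7 = 285.7, so 286 (143 per arm). This does not match; the gap is 286 − 260 = 26 subjects.

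**Step 2. What 260 delivers.**
- 260 × 0.7 = 182, or 91 per arm: 18 short in total, 9 short per arm.
- Largest drop-out that still leaves 200: 1 − 200/260 = 23.1%.

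**Step 3. Reproduce the base figure of 100 per arm.** Two independent means, standardised SD of 1: n per arm = 2(z_α + z_power)² ÷ d².
- One-sided 5%: 2 × (1.645 + 0.842)² ÷ 0.35² gives 101 after rounding up (102 by the t-test). This nearly reproduces 100.
- Two-sided 5%: 2 × (1.960 + 0.842)² ÷ 0.35² gives 129 after rounding up (130 by the t-test). This does not reproduce 100.

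**Step 4. Power at 100 and at 91 per arm.** Normal approximation: power = Φ(d√(n/2) − z_α).
- n = 100: 0.35 × √50 = 2.475.
- n = 91: 0.35 × √45.5 = 2.361.

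| Test at 5% | Method | 100 per arm | 91 per arm | Loss from the slip |
|---|---|---|---|---|
| One-sided | normal | 0.797 | 0.763 | 3.4 points |
| One-sided | t-test | 0.794 | 0.760 | 3.4 points |
| Two-sided | normal | 0.697 | 0.656 | 4.1 points |
| Two-sided | t-test | 0.692 | 0.651 | 4.1 points |

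**Step 5. Attribute the gap to 80% (t-test).**
- One-sided: 0.800 − 0.794 = 0.6 points from the base figure, and 3.4 points from the drop-out step.
- Two-sided: 0.800 − 0.692 = 10.8 points from the base figure, and 4.1 points from the drop-out step.

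**The case against.** **Nobody is lost from the analysis.** Under intention to treat with imputation all 260 are analysed, so the shortfall is in observed outcomes, not in analysed subjects. The Safety of subjects section schedules the BSS and BDI every two weeks in both arms during the first six weeks. If those scores fed the imputation model, a subject with an interim score but no later one would contribute partial information. This stands in part: counting all 78 expected drop-outs (260 × 0.3) as uninformative makes 91 per arm a conservative figure. But imputation does not in general replace unobserved outcomes in full, and the Sample size section sets its requirement and then adds a drop-out allowance without relying on imputation.

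**130 per arm gives 80% power two-sided.** It does (0.803 by the t-test), but only with no drop-out. The text says that 260 already includes the 30% allowance, so the match is a coincidence and does not support the stated derivation.

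**A baseline-adjusted analysis would need fewer subjects.** If the baseline correlation were 0.5, which is an assumption, about 97 per arm would suffice two-sided. The Statistical analyses section describes no such adjustment and the article gives no correlation for it. Adjustment would also leave the drop-out step wrong.

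**A stronger reading.** A reader might infer that the drop-out slip takes power from 80% to 65%. The figures do not support that. With a two-sided test, power is already 69% at the stated 100 per arm, before any allowance is considered. Most of that gap belongs to the base figure and the unstated sidedness, which is a separate matter.

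**Conclusion.** The drop-out step is wrong as written. At the plan's own 30%, 260 randomised leaves about 91 observed outcomes per arm against a stated need of 100. The total meets that need only if drop-out is 23% or less, and at 30% the need would take 286 randomised.

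The attributable cost is modest: 3.4 power points one-sided or 4.1 two-sided at d = 0.35. This assumes an unadjusted comparison of two means, equal drop-out in the arms and no information recovered through imputation. The remaining two-sided shortfall from 80% is not due to this slip. Nor does the slip by itself bias the treatment estimate or call for a change to the design.

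**What to change.** Keep 260 and correct the Sample size text so that it:

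1. states that 260 randomised gives about 91 observed outcomes per condition at 30% drop-out, and 100 per condition only if drop-out is 23% or less;
2. states whether the 5% test is one-sided or two-sided;
3. gives the matching unadjusted power for d = 0.35 at 91 per arm: 76% one-sided or 65% two-sided;
4. notes that imputation using the interim BSS scores may recover part, but generally not all, of the information lost.

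If the test is two-sided, the sentence giving 100 per condition must be revised at the same time. Otherwise the corrected power would stand beside a base figure that an unadjusted two-sided test does not reproduce (about 130 per arm needed).

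The cost is wording only, with no added subjects and no change to conduct. Holding to 100 observed outcomes per arm at 30% drop-out would instead mean randomising 286, which is 26 more.
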